## PROPOSAL ABSTRACT:

|                                        |                                                                                                                                              |
|----------------------------------------|----------------------------------------------------------------------------------------------------------------------------------------------|
| Name of Principal Investigator: | [name]                                                                                                                    |
| Proposal Title:                 | Effectiveness of a hybrid exercise-based cardiac rehabilitation program. Randomized, multicenter, and non-inferiority clinical trial. |

**Background:** Cardiac rehabilitation programs are designed as a secondary prevention intervention in patients surviving cardiovascular events. These programs are widely established, and their effectiveness and cost-effectiveness proven, given they reduce cardiovascular mortality and subsequent hospitalizations. In spite of this, this intervention remains underutilized, not only because of low patient referral, but also because of the scarcity of existing programs (especially in middle and low resource settings such as the Latin American context). As cardiovascular disease is the condition that produces the highest mortality and disability-adjusted life-years in the world, with major subsequent impact on the countries' economies, there is an urgent need to create more accessible delivery models of cardiac rehabilitation programs in order to increase the efficiency of health systems and improve population health.

**Hypothesis:** A hybrid exercise-based cardiac rehabilitation model, which include 10 face-to-face sessions plus distance monitoring through text messages and phone calls is not inferior in effectiveness to the standard model.

**General goal:** To evaluate if an abbreviated exercise-based cardiac rehabilitation program is not inferior to the standard exercise-based cardiac rehabilitation program.

### Specific goals:

**Primary goal:** To evaluate if the prevention of recurrent cardiovascular events is not inferior in the hybrid exercise-based cardiac rehabilitation programs in comparison to the standard program.

### Secondary goals:

- To compare the effectiveness of the abbreviated cardiac rehabilitation programs with the standard program in terms of:
  - o cardiovascular risk factor control (dyslipidemia, hyperglycemia, hypertension, obesity)
  - o exercise capacity
  - o adherence to physical activity recommendations
  - o adherence to diet recommendations
  - o health-related quality of life
  - o exercise related adverse events

**Methodology:** A non-inferiority, pragmatic, multicenter, parallel, single blinded, randomized clinical trial will be conducted. 314 patients with coronary artery disease including Acute Coronary Syndrome (Unstable Angina, Myocardial infarction with or without ST elevation) or stable coronary vessel disease diagnosed by coronariography or stress test, who have received medical treatment, thrombolysis, angioplasty or revascularization surgery will be recruited consecutively, with written informed consent. Participants will be assigned to experimental or standard rehabilitation programs using a permuted blocked randomization scheme. Concealment of assignment will be preserved. The experimental cardiac rehabilitation program includes medical evaluations, 10 face-to-face exercise sessions, diet and smoking counseling, and distance monitoring with text messages and phone calls, delivered by a physiotherapist. The standard cardiac rehabilitation consists of medical evaluation, 20-24 face-to-face exercise sessions, as well as education sessions about diet and smoking, delivered by a nurse, nutritionist and physiotherapist. The main outcome is a composite of cardiovascular mortality and hospitalizations due to cardiovascular causes (non-fatal stroke, non-fatal myocardial infarction, heart failure, and need of revascularization surgery). Secondary outcomes are cardiovascular risk factor control, exercise capacity, adherence to physical activity and diet recommendations, health-related quality of life and exercise-related adverse events. The outcomes will be measured at the end of intervention, at 6 months, and at 12 month follow-up from recruitment. Only main outcome will be a maximum of three year of follow-up. The sample size was calculated considering 5% of non-inferiority limit. Per protocol and intention to treat analysis will be considered. A survival analysis will be run for the primary outcome. One interim analysis is planned when 50% of patients have completed the evaluation at the end of the first year of follow-up.

**Expected results:** We anticipate that if non-inferiority is demonstrated, a more suitable and affordable model of cardiac rehabilitation will be available for patients and the health system, to increase coverage, save resources, and improve cardiovascular health indicators.

[figure not shown]

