#### 4.3. Sample size.

If there is a true difference in favour of the hybrid exercise-based cardiac rehabilitation of 7% in hospitalization rate, then 254 patients are required (127 per group) to be 80% sure that the upper limit of a one-sided 97.5% confidence interval will exclude a difference in favour of the standard exercise-based cardiac rehabilitation group of more than 6%. Considering anticipated loss of follow-up (10%) and the inclusion of an interim analysis that penalizes the power (interim analysis adjustment using Pocock boundary), 314 patients will be recruited (157 per group).

[figure not shown]

This sample size considered the hospitalization and cardiovascular mortality outcomes that was reported in the systematic review by Anderson in 2016 (14), which totaled 18% in the first year of follow-up in those randomized to exercise-based cardiac rehabilitation. The non-inferiority margin was established as is suggested by the Food and Drugs Administration (FDA) (31), which is 50% of the difference between the standard or current therapy (i.e., standard cardiac rehabilitation) and the placebo (or usual care) obtained from a meta-analysis, in this case the same by Anderson (12%).

65

66

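### The abstract says the sample size used a 5% non-inferiority limit, but section 4.3 sizes the same trial on 6%

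*Protocol*

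**What the plan says.** **Proposal Abstract, Methodology paragraph.** After giving the trial size as 314 patients, it states: "The sample size was calculated considering 5% of non-inferiority limit". It gives no derivation.

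**Section 4.3, Sample size.** The margin used for sizing is 6%: the bound of interest "will exclude a difference in favour of the standard exercise-based cardiac rehabilitation group of more than 6" per cent. Power is set at 80% and the interval is one-sided at the 97.5% level. The planning assumption is: "If there is a true difference in favour of the hybrid exercise-based cardiac rehabilitation of 7% in hospitalization rate". The result is "254 patients are required (127 per group"), raised to 314 for 10% loss to follow-up and a Pocock-adjusted interim analysis. The event rate comes from a cited systematic review, "which totaled 18% in the first year of follow-up in those randomized to exercise-based cardiac rehabilitation". The margin rule is also given, "which is 50% of the difference between the standard or current therapy (i.e., standard cardiac rehabilitation) and the placebo (or usual care"), with the difference taken from that same review and shown in brackets as 12%.

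**Section 4.7, item 6.** The primary comparison is estimated as an absolute risk difference and a relative risk, with a hazard ratio in addition. Non-inferiority requires the intention-to-treat and per-protocol analyses to agree. No margin is repeated there.

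**The concern.** Both statements describe one calculation for one trial, and they give different limits. Each sentence is complete and current, and neither is in a log of changes. The 5% cannot be a significance level, because the abstract calls it a non-inferiority limit and section 4.3 works with a one-sided 97.5% interval. It is not a rounding of 6% either.

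In a non-inferiority trial the margin decides the primary conclusion. With two values on record, a result whose upper limit falls between 5 and 6 points could be called a success or a failure, and the choice could be made after the data are seen. Someone who reads only the abstract would also judge the trial against a different standard from someone who reads section 4.3.

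**Working it through.** **Inputs from section 4.3.** Standard-arm rate 18%; true difference 7 points in favour of hybrid, hence 11% in the hybrid arm; one-sided 0.025; power 80%; 10% loss; one Pocock interim look. The margin M is 6% (section 4.3) or 5% (abstract).

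**Step 1: the margin rule.** 0.50 × 12% = 6%. The stated rule gives the section 4.3 value, not the abstract's.

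**Step 2: the stated sample size.** The unpooled formula per group is

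n = (1.960 + 0.842)² × [p_S(1 − p_S) + p_H(1 − p_H)] / (M + p_S − p_H)², where the first factor is 7.849.

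At 18% v 11% the variance term is 0.1476 + 0.0979 = 0.2455.

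| Rates | Margin | n per group | Total |
|---|---|---|---|
| 18% v 11% | 6% | 7.849 × 0.2455 / 0.13² = 114.02, so 115 | 230 |
| 18% v 11% | 5% | 7.849 × 0.2455 / 0.12² = 133.8, so 134 | 268 |
| 20% v 13% (assumed) | 6% | 7.849 × 0.2731 / 0.13² = 126.8, so 127 | 254 |
| 20% v 13% (assumed) | 5% | 7.849 × 0.2731 / 0.12² = 148.9, so 149 | 298 |

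At the stated rates the plain formula gives 254 under neither margin. With a continuity correction, 18% v 11% gives 129 per group (258) at 6% and about 302 in total at 5%. The exact 127 at 6% needs 20% v 13%, which the Protocol does not state. A 5% margin also reaches 127, at an equally unstated 17.1% v 10.1%.

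**Step 3: the inflation.** For two equally spaced Pocock looks (critical value 2.178) the inflation factor is 1.110. Then 254 / 0.90 × 1.110 = 313.3, which agrees with the stated 314. The same steps from 268 give 268 / 0.90 × 1.110 ≈ 331.

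**Step 4: power with 127 per group.** Power = Φ[(M + p_S − p_H)/SE − 1.96].
- 18% v 11%: SE = √(0.2455/127) = 0.04397. At 6%, Φ(0.997) = 84.1%. At 5%, Φ(0.769) = 77.9%.
- 20% v 13% (assumed): 80.1% at 6% and 73.5% at 5%.

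**Step 5: a result that splits the margins.** Take 157 per arm, complete follow-up, 24 hybrid and 28 standard events.
- Rates 15.29% and 17.83%; difference −2.55 points.
- SE = √[(0.1295 + 0.1465)/157] = 0.04193.
- Wald upper limit = −0.0255 + 1.96 × 0.04193 = 5.67%, which passes at 6% and fails at 5%.

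If the Pocock value 2.178 were applied instead, this result would give −0.0255 + 0.0913 = 6.58% and fail under both. But 23 v 28 events would then split them: difference −3.18 points, SE 0.04159, upper limit −0.0318 + 0.0906 = 5.87%. A stricter critical value changes which results fall between the two limits, not the existence of the gap.

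**The case against.** The strongest reply is that the Protocol already shows which figure is meant. Section 4.3 is the operative section, it states 6% as the limit to exclude, and its rule yields 6%. The abstract's 5% is a single sentence without support. This stands, and it rules out the tempting reading that nothing in the document settles the margin. It does not remove the conflict, because the 5% sentence remains part of the Protocol and describes the same calculation.

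A reader might also infer that 254 patients can be obtained only with 6%. The arithmetic does not support that. At 18% v 11% the plain formula gives 230 at 6% and 268 at 5%, and 268 is the nearer to 254. An exact match needs an unstated rate under either margin. The case for 6% rests on the stated limit and the half-of-12% rule.

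Third, the loss of power is modest at the stated rates: 77.9% is about 2 points below the 80% target. With 141 per arm (157 less 10%), power at 5% is still 82.0% before any Pocock adjustment. The larger figure of 73.5% depends on the assumed 20% v 13%. Power when the two programmes are truly equal is a separate question about the assumed 7-point benefit, and it is not part of this point.

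Last, repeating the margin in section 4.7 is commonly left to a statistical analysis plan, which is not at hand. Its absence there is therefore not a fault in itself. It means only that section 4.7 does not resolve the discrepancy.

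**Conclusion.** The point holds. The Protocol gives two values, 5% and 6%, for the threshold that decides its primary conclusion. Its own derivation favours 6%, so the abstract is most likely in error.

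The main consequence is the one-point zone in which the verdict reverses. The effect on size and power is secondary: 84.1% against 77.9% with 127 per group, and about 331 instead of 314 recruited if 5% were meant. Those figures assume 18% v 11%, the unpooled formula and one-sided 0.025, with no interim adjustment in the power values. Under the assumed 20% v 13% the power values are 80.1% and 73.5%. The correction should be made because the margin is the decision rule, even though it is small and its direction is fairly clear.

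**What to change.** Before unblinding:

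1. Correct the abstract's Methodology paragraph to the 6% margin used in section 4.3.
2. In section 4.7 item 6, name 6% on the absolute risk difference (hybrid minus standard) as the limit that the upper bound of the one-sided 97.5% confidence interval, or the interim-adjusted bound if one applies, must exclude in both the intention-to-treat and the per-protocol analysis.

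The cost is one corrected line and one added sentence. The sample size does not change, because section 4.3 already sizes the trial on 6%.

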## PROPOSED RESEARCH

### 1. Background.

#### 1.1. Cardiovascular disease. Epidemiology and disease burden.

Cardiovascular disease (CVD) is the leading cause of morbidity and mortality in the world, of which ischemic cardiomyopathy produces the highest mortality and disability-adjusted life-years (1). In the Americas, CVD contributes to 33.7% of total deaths (2) and it is estimated that the number of deaths in the region attributable to CVD will increase by more than 60% from the year 2000 to 2020, compared with an increase of only 5% in the developed world (3). Specifically in Latin America and the Caribbean, ischemic heart disease is the predominant form of CVD, with an adjusted mortality of 66.4 per 100,000 persons (4). In Chile, CVD accounts for 66.7% of diseases, making it the second most common condition, for which the most life-years are lost due to premature death (5).

#### 1.2. Secondary Prevention. Purpose, elements and goals achievement.

Once CVD has been established, the fundamental objective is to prevent mortality, recurrent cardiovascular events, and other complications through secondary prevention programs that include drug therapy, healthy lifestyle education, and control of risk factors such as high blood pressure, cholesterol, as well as diabetes mellitus(6,7). While these recommendations are widely known, their achievement is not as expected, as evidenced by the Prospective Urban Rural Epidemiology (PURE) study which reported that only 35.1% (95%CI, 29.6% - 41.0%) of patients maintain high levels of physical activity; 39.0% (95%CI, 30.0% - 48.7%) follow a healthy diet; and 18.5% (95%CI 17.6% - 19.4%) continue smoking despite a cardiovascular event. The achievement of these heart-health goals is even lower in low-income countries (8). This scenario is reproduced in the South American region and in Chile, where it has been reported that 50% of patients suffering a myocardial infarct achieve 4 of 8 established goals, the worst being having a normal body mass index (BMI) (22%) and performing physical activity (23.9%) (9).

To achieve the secondary prevention goals, the interventions currently in use need to be implemented through formal programs that promote healthy lifestyle as well as adherence to medical recommendations and drug therapy. One intervention that is recommended by international guidelines is Cardiac Rehabilitation (10,11), which is an efficient, comprehensive way to deliver secondary prevention and promote better outcomes.

#### 1.3. Cardiac Rehabilitation. Effectiveness, cost-effectiveness, availability, and barriers.

Cardiac rehabilitation programs include medical evaluation, education, counselling, and prescription of exercise as their key components (12). Guidelines for cardiac rehabilitation strongly recommend supervised exercise / individually-prescribed physical activity, based on high-level evidence which support effectiveness. The exercise programs in these clinical guidelines including similar characteristics: long programs of at least two or three months duration, with two to five exercise sessions per week, consisting of low to moderate intensity aerobic training combined with resistance exercises in sessions between 30 to 60 minutes (13).

The most rigorous systematic review that evaluates cardiac rehabilitation, which included 63 clinical trials comprised of 14,486 randomized patients, demonstrates that it reduces cardiovascular mortality (RR=0,74; CI95% 0,64 to 0,86) and recurrent hospitalization (RR=0,82; CI95% 0,70 to 0,96), and improves quality of life. The benefits in outcomes were independent of patients' specific diagnosis, type of cardiac rehabilitation (exercise only vs comprehensive rehabilitation) dose of exercise, length of follow-up, trial publication date, setting (center vs home-based), study location (continent), sample size and risk of bias (14).

Despite this knowledge, there are barriers to delivery of exercise-based cardiac rehabilitation programs. Indeed, cardiac rehabilitation is under-utilized (including in Chile) when compared with other recommended secondary prevention interventions, such as medication. The barriers to delivery of cardiac rehabilitation programs include those that are patient-oriented (e.g., patient refusal), provider-oriented (e.g., provider fails to refer patient to cardiac rehabilitation), and others that are related to the health care system (e.g., lack of a cardiac rehabilitation programs, lack of insurance coverage, etc.) (12). Indeed worldwide, only 38.8% of countries have cardiac rehabilitation programs. Specifically, 68% of high-income and 23% of low/middle-income countries offer cardiac rehabilitation programs to patients with CVD (15). In Chile, the

[figure not shown]

43

44

existing cardiac rehabilitation programs cover only 5% of patients who need them, and these programs are mainly in the private system and in the country's capital (16). This is a very similar situation to that of other Latin American countries (17), revealing major inequalities of access.

Since one of the barriers to delivery is the cost of implementation of cardiac rehabilitation programs, economic evaluations of cardiac rehabilitation have been conducted, across many different settings. A systematic review that included 22 such economic evaluations supported the implementation of this service (18). Another review, which includes studies from low- and middle-income countries, shows only two cost-effectiveness evaluations in Latin America, only in patients with heart failure. These reports from Brazil (19) and Colombia (20) show that cardiac rehabilitation is highly cost-effective, but the review authors are emphatic in concluding that given the countries' limited budget, affordable models need to be designed, especially for countries or settings with low income levels (21).

Specifically in Chile, our group conducted a cost-utility analysis which concluded that, considering the cost-effectiveness threshold of 1 Gross Domestic Product per capita, exercise-based cardiac rehabilitation is highly cost-effective for the public health system, and should be the standard of care cardiovascular secondary prevention. In this study, a standard model of exercise-based cardiac rehabilitation (as evaluated in the Cochrane Systematic Review by Anderson) resulted in an incremental cost-effectiveness ratio (ICER) of US\$ 722.34 (CL\$ 480,359.66) per quality-adjusted life year (QALY), compared with that of standard care (FONIS SA14ID0005).

One aspect that is necessary to consider, which we grappled with in our economic evaluation, is that one element that introduce structural uncertainty in the modelling process is the configuration of the cardiac rehabilitation service; the costs differ in different regions, countries and settings, and the effectiveness could vary as well. Indeed, the variability in the cost of cardiac rehabilitation delivery is wide around the world. According to a recent review, costs ranged from US\$294 in the United Kingdom to US\$12,409 in Italy in high-income countries, and from US\$146 in Venezuela to US\$1,095 in Brazil in middle-income countries. These differences were explained principally by differences related to facilities, personnel involved, and session dose (all values in this review are standardized according to purchasing power parity) (22). In our economic evaluation, we valued standard exercise-based cardiac rehabilitation in Chile at US\$102.07, this did not consider pharmacologic therapy (because it is considered usual care), which would increase the cost near to US\$1,500.

45

#### 1.4. Cardiac Rehabilitation Models.

Several approaches to lowering the cost and increasing accessibility of cardiac rehabilitation have been described, such as delivering the interventions in unsupervised settings, using information and communication technology, task-shifting to lower-cost healthcare personnel, and offering a lower dose (i.e., fewer sessions). Other strategies include using lower-cost exercise equipment, and ceasing ECG-monitoring during exercise sessions (22,23). The way that these strategies are implemented in the programs formulates several alternative models to the traditional cardiac rehabilitation.

A systematic review characterized these models, and evaluated their effectiveness against traditional supervised programs. From 8 broad categories of alternative models identified, two were shown to be effective. First, the multifactorial individualized telehealth model produced similar reductions in cardiovascular risk factors compared with traditional programs; however there is a lack of cost-effectiveness data and information about harder outcomes such as re-hospitalizations and subsequent cardiac events. Second, the community or home-based cardiac rehabilitation models were shown to result in minimal differences with traditional programs in terms of mortality and cardiovascular event rates (24).

One strategy increasingly proposed and used is delivery of cardiac rehabilitation via the internet. Considering its newness however, availability and quality of evidence demonstrating effectiveness is low when compared with the high-quality evidence that support the effectiveness of traditional programs, or even through personal contact via telephone using coaching (24,25).

Besides these several settings approaches, and considering resources and task-shifting, countries such as the Netherlands and United Kingdom, recommend that a general physician, exercise physiologist, physiologist, physiotherapist, allied healthcare provider, or another staff member trained in exercise prescription would be sufficient to supervise exercise sessions (26,27).

46

47

48

[figure not shown]

The most recently-proposed model is that designed by the International Council of Cardiovascular Prevention and Rehabilitation (ICCPR) entitled Cardiac Rehabilitation Delivery Model for Low-Resource Settings. Therein, strategies to deliver all core components of cardiac rehabilitation, but adapted to low-resource settings are recommended. In this proposal there is an algorithm for cardiac rehabilitation delivery based primarily on availability of healthcare personnel. In the second scenario of this algorithm, how each component of cardiac rehabilitation (e.g., assessment, lifestyle management, medical management, and structured exercise) can be delivered by an allied healthcare worker (e.g., physiotherapist) is outlined, and the approaches proposed are feasible to implement in a non-hospital environment. Additionally, this consensus statement offers direction for adaptation according to setting, including mobile technology (23). In our economic evaluation, we generated a third model in order to evaluate the cost-utility of this Model for Low-Resource Settings. The value of one entire program for one patient resulted in US\$46.16, which is 45% cheaper than the Standard Model; however effectiveness data is not yet available considering the consensus is quite recent, thus we had to run probabilistic analysis using the effect reported for the Standard Model resulting in considerable uncertainty in our conclusions.

